D.5.2.8. Legal Services: South Africa's legal environment concerning both the rights of those infected with HIV/AIDS and the rights of women has been cited by many scholars as a potential model for other countries on the continent Csetse, J. 2003. Human Rights Watch. Policy Paralysis: A call for action on HIV/AIDS related human rights abuses against women and girls in Africa.. Despite the favourable legislation, there is a gap in application, where the majority of those infected with HIV or most at risk for HIV infection do not know that such legal protection exists. Even those individuals who know their legal rights often face barriers to enforcing them. These barriers can include issues of access in terms of availability, location and cost. In general, the legal system is largely unavailable to a majority of the population, a notion reiterated by a conference co-hosted by the AIDS Law Project in February, 2006. The group identified a number of barriers HIV infected individuals face to seeking justice, two of which include lack of information about the content of human rights as well as the inaccessibility of legal services Consensus Statement on Improving Access to legal services for people living with HIV/AIDS. Conference on HIV and access to legal services, held at WITS University February 17-18th, 2006. Retrieved January 22, 2007 from http://dedi20a.your-server.co.za/alp/images/upload/Consensus.pdf..  It is evident through multiple calls to action that increasing access to legal rights education and facilitating access to legal services for the poor are two unmet needs that could potentially affect the spread of infection as well as decrease the number of violations of HIV positive women's rights within South Africa.  We hope to respond to these calls to action through an intervention that will provide an enhanced package of HIV post test support services to women attending antenatal care (ANC) at Umlazi Section D Clinic. Legal education and services will be integrated with other HIV post test support services for women as part of this package. The primary aim of the legal component is twofold: 1) To increase pregnant women's understanding of their legal rights, and 2) To facilitate their access to legal support services 

Women in the intervention arm will be exposed to the legal education and access component at 3 different times while they are attending the clinic. 

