Monitoring and Evaluation - This study represents an ideal opportunity for the faculties of Medicine and Law to collaborate on a comprehensive intervention that can be rigorously evaluated through a randomized controlled trial design. We firmly believe that integrating services will result in better health outcomes for women, and we propose to document the impact of these comprehensive services for women through this intervention trial. We describe below some of the benefits we foresee to this collaborative partnership between the Faculty of Medicine and Law.
(1)  Documenting women's legal needs: 
o	Our pre and post evaluation assessment will allow us to measure knowledge of legal rights, knowledge of legal recourse, perceived legal need, and experiences of discrimination of the 1,495 women who will participate in our study. 
o	We anticipate that the baseline assessment will yield strong empirical evidence documenting current levels of legal awareness and need within a large sample of individuals in the province. 
(2) Evaluating the impact of providing legal education and services: 
o	We will measure the impact of the legal education component by comparing women's scores on legal questions on both the baseline and follow up measure. We will do this for each of the legal questions that are asked in the baseline survey. In this way, we will be able to evaluate if the legal component of the program increased women's understandings of their own rights.
o	We propose to document how legal services impact women through a case study approach. The case study approach that we are proposing will complement the quantitative data. We will select and follow prospectively women who have received legal services through the intervention to describe in depth how they utilized the legal services and what impact it had on them.  
(3) Describing the process of providing legal services. 
Through the process evaluation component of our intervention trial we will also be able to document the following: 
o	the number of women given legal referrals by our Research Nurses
o	the number of women meeting with law staff at UKZN clinic
o	the number of women seeking legal recourse 

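### The only analysis written for the legal-awareness scores is a before-after comparison with no arm contrast, which conflicts with the randomised comparison implied by Aim 2 and D.11

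*Protocol*

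**What the plan says.** The method is in Protocol D.5.2.8 (Legal Services), Monitoring and Evaluation, item (2). Impact is measured by comparing women's "scores on legal questions on both the baseline and follow up measure". On scope it adds: "We will do this for each of the legal questions that are asked in the baseline survey". It then draws a causal conclusion: "we will be able to evaluate if the legal component of the program increased women's understandings of their own rights". No study arm is mentioned in these sentences, and neither follow-up visit is specified.

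Other text bears on how to read this:

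- **Who receives the component.** D.5.2.8: "Women in the intervention arm will be exposed to the legal education and access component at 3 different times". The comparison arm's 6- and 10-week sessions are about infant health (D.7, Table 1).
- **Who answers the questions.** The pre and post assessment covers legal knowledge, need and "experiences of discrimination of the 1,495 women who will participate in our study", so both arms are measured.
- **Stated design.** The opening of the same Monitoring and Evaluation text calls this a "comprehensive intervention that can be rigorously evaluated through a randomized controlled trial design".
- **Aims.** The legal outcomes are item 2.4 of Aim 2, whose purpose is to determine the intervention's independent effect in a randomised trial.
- **Analysis section.** D.11 compares women randomised to standard or enhanced counselling on the primary outcomes of Aim 2, separately by HIV serostatus. Its three hypotheses cover sexual risk, mother-to-child transmission risk and psychosocial outcomes, and none is legal.
- **Outcome definitions.** D.8 defines no legal outcome, and Table 4 gives no detectable difference for one.

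**The concern.** A before-after difference in women who received the component estimates the component's effect plus everything else that moved their answers. Here that includes having been asked the same questions before (surveys are at baseline, 14 weeks and 9 months postpartum), ordinary experience of the clinic and of childbirth, and any change in public awareness. Most women start antenatal care at about 28 weeks (D.2.1), so roughly a year passes before the last survey. Randomisation removes these shared influences, but only if the arms are compared. A shared fall in scores would do the reverse and hide a real effect.

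At stake is the legal-awareness part of Aim 2.4. The protocol would be answering a randomised question with a non-randomised estimate, although the control data will be in hand.

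**Working it through.** **1. Is there a figure to reproduce?** No. The protocol gives no sample size, power or effect size for any legal outcome. The per-arm numbers used below (279 HIV-positive, 295 HIV-negative, together 574) come from D.9.3. They match Table 3 with a pooled two-proportion formula, two-sided alpha 0.05 and 80% power (power is not stated there, so 80% is assumed).

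**2. The texts side by side.**

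| Place | Contrast implied | Specific to the legal scores? |
|---|---|---|
| D.5.2.8, M&E item (2) | Baseline against follow-up, no arm | Yes |
| D.5.2.8, M&E opening | Randomised evaluation | The collaborative intervention in general |
| Aim 2 with 2.4 | Independent effect in a randomised trial | Lists the legal outcomes, gives no analysis |
| D.11 general rule | Randomised arms, by serostatus | No; covers Aim 2 primary outcomes |
| D.11 hypotheses, D.8, Table 4 | None | Legal outcomes absent |

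The specific text and the general text point in different directions, and only the specific text says what will be done with the legal scores.

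**3. What the literal method would do.** Take one legal question scored correct or incorrect, no true intervention effect, and a gain d shared by both arms. Let D be the proportion of women whose answer changes in either direction, and n the women tested in the intervention arm. With a McNemar-type normal approximation at two-sided alpha 0.05, the probability of declaring an increase is

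P = Φ{ [d − 1.96·√(D/n)] / √[(D − d²)/n] }.

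The documents supply n and alpha. **d and D are assumptions.** For d = 0.05 and D = 0.30:

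- n = 574: 1.96·√(0.30/574) = 0.0448; denominator √(0.2975/574) = 0.0228; (0.05 − 0.0448)/0.0228 = 0.23; P = 59%.
- n = 295: 1.96·√(0.30/295) = 0.0625; denominator 0.0318; ratio −0.39; P = 35%.
- n = 279: 1.96·√(0.30/279) = 0.0643; denominator 0.0327; ratio −0.44; P = 33%.

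Range over the assumptions:

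| n | d = 3 points, D = 30% | d = 5, D = 30% | d = 10, D = 30% | d = 5, D from 40% to 20% |
|---|---|---|---|---|
| 279 | 15% | 33% | 87% | 26% to 46% |
| 295 | 15% | 35% | 88% | 27% to 48% |
| 574 | 26% | 59% | 99% | 47% to 77% |

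A second parameterisation (50% correct at baseline, within-woman correlation 0.3 to 0.5, both assumed) gives similar results for a 5-point gain: 29% to 39% (n = 279), 31% to 41% (n = 295) and 53% to 67% (n = 574).

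**4. The between-arm comparison.** With the same shared gain, both arms have follow-up proportion p + d, so the expected difference is (p + d) − (p + d) = 0. The two-sided rejection rate stays at 5%, half of it in the favourable direction, whatever d is.

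**5. Precision after the change.** From an assumed 50% correct, 80% power detects a difference of about 11.8 points with 279 per arm, 11.5 with 295 and 8.3 with 574. The stratum figures are close to the 8 to 12 points that Table 4 lists for other outcomes.

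**The case against.** The strongest reply is that the protocol as a whole does intend a randomised comparison. Aim 2 is the randomised aim and 2.4 belongs to it, D.11 sets a between-arm rule for Aim 2, and the legal section itself appeals to the randomised design. The disputed sentence sits in the intervention section, in a list of foreseen benefits of a collaboration, and names no test. D.11 also speaks of change from before to after the intervention while comparing arms, so the sentence could be shorthand for comparing change between arms, and an analysis plan could say so.

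Much of this stands. A reader might infer that the protocol rejects the randomised comparison for Aim 2.4. It does not: the general text supports one, so the defect is a conflict to reconcile. But the sentence is no mere omission left for later. It states a method and a causal conclusion, its plain reading is before against after, and D.11's hypotheses do not include the legal outcomes.

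Three further inferences are not supported:

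- **Regression to the mean.** It does not shift the average of a cohort that was not selected on the score, and the eligibility criteria in D.4.1 include no legal-knowledge criterion.
- **Multiplicity.** The comparison is made for each question, but no significance test or claim rule is stated.
- **Pooling both arms before and after.** Nothing in the protocol proposes it.

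**Conclusion.** The point holds as a conflict between the one analysis written for the legal scores and the randomised design stated elsewhere. Read literally, the D.5.2.8 sentence cannot support the conclusion attached to it, because gains shared by both arms would count as an effect of legal education.

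How large the error would be cannot be derived from the documents. The illustration (59% with 574 women, 33% to 35% within a serostatus stratum, against 5%) rests on an assumed 5-point shared gain and 30% discordance. The stratum figures are the more relevant, since D.11 analyses the serostatus groups separately. With no shared gain, the before-after test also holds its 5% level.

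Severity is moderate. A reader might take this to threaten the trial's main conclusions, but it does not reach the STI, PMTCT or psychosocial outcomes. The legal outcomes are not in D.8, Table 4 or the hypotheses, and STI incidence drives the sample size. The data for a valid comparison will exist either way, so nothing is lost if the text is corrected before analysis.

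**What to change.** In D.5.2.8, Monitoring and Evaluation item (2), replace the before-after sentence with text to this effect: the effect of the legal component on the legal-question scores will be estimated by comparing follow-up scores between the randomised arms, adjusted for the baseline score, within HIV-serostatus strata as in D.11; within-arm change from baseline will be reported descriptively only. Name the follow-up visit; D.11 uses 9 months for its hypotheses. Add a cross-reference in D.11 so that the two sections agree.

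A summed awareness score is not needed to cure the flaw; the protocol defines none, and the between-arm contrast can be applied to the questions as asked. The change covers only the legal questions asked at both times. Other items in 2.4, such as uptake and outcome of legal assistance, are outside this sentence.

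The cost is one or two sentences. The planned surveys already ask the legal questions in both arms, so no extra participants, visits or items are required.

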(1)	To describe the demographic, social and psychological factors that affect sexual risk behaviors, partner uptake of VCT, family planning intention, infant feeding choices, and HIV serostatus disclosure to sexual partners, among HIV-positive and HIV-negative women attending the Umlazi Section D ANC clinic in Durban, South Africa. 

(2)	To conduct a randomized controlled trial of HIV VCT plus enhanced posttest support as compared to standard HIV VCT among HIV-positive and HIV-negative pregnant women in the Umlazi Section D ANC clinic to determine the independent effect of the intervention on the outcomes listed below, and to determine whether HIV-serostatus to sexual partners influences these intervention effects:
2.1 	Sexual risk of HIV as measured by:  STI incidence (Trichomonas vaginalis, Neisseria gonorrhea and Chlamydia), consistent and correct condom use among HIV-positive and HIV-negative women; and partner uptake of HIV VCT among HIV-positive women.  
2.2. 	Factors that affect mother-to-child transmission of HIV including: acceptance of HIV VCT among HIV-positive and HIV-negative women; acceptance of ARVs, adherence to national infant feeding guidelines, and family planning use among HIV-positive women.
2.3. 	Psychosocial outcomes of PMTCT participation as measured by: perceived social support, emotional distress and partner violence among HIV-positive and HIV-negative women.  
2.4 	With the addition of the legal education and referral component to the intervention study, we will also measure women's awareness of legal rights, awareness of legal recourse, perceived legal needs, uptake of legal assistance and outcome of seeking legal assistance within the 12 month study period. 

(3)	 Additionally, our secondary aim is to compare the following operational outcomes across study arms:  (a) counseling time required; (b) the proportion of women returning for ongoing counseling at 6 and 10 weeks; (c) client's perceived quality of services; (d) the cost of service provision and opportunity costs incurred by clients.
   

Our collaboration includes a multidisciplinary team of researchers from the U.S. and South Africa who will join efforts to test a culturally appropriate and feasible intervention designed to overcome limitations and expand the preventive health benefits of PMTCT programs. Results from this intervention study will be generalizable to other regions of sub-Saharan Africa that are faced with similar challenges related to HIV prevention.

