The second primary aim of the study is to conduct a randomized controlled trial of HIV enhanced post-test support as compared to standard HIV counseling among HIV-positive and HIV-negative women in the Umlazi Section D ANC clinic.  To do this we will randomize 1,495 women at Umlazi Section D ANC in Durban, South Africa to either a comparison or an intervention arm. Women randomized to the comparison arm will receive the standard WHO/CDC HIV pre-and post-test counseling and will have brief follow-up sessions with counselors 6- and 10-weeks postpartum. Women randomized to the intervention arm will receive: 1) a health education video immediately prior to HIV pre-test counseling; 2) pre and post-test counseling sessions that build on the standard protocols by providing more risk reduction counseling, more counseling on disclosure, and PMTCT-related decisions; 3) two additional post-test counseling sessions that coincide with the 6- and 10-week postpartum visits and focus on legal education and referral, partner testing, sexual behavior change and family planning; 4) an active referral to post-test support groups and 6) access to onsite legal support. Women in both arms will be administered a baseline survey at enrolment. Post-intervention assessment will occur at 14 weeks and 9-months post-partum. We will examine the independent effect of the intervention on primary outcomes related to sexual risk transmission of HIV, factors that affect mother-to-child transmission, and psychosocial outcomes of PMTCT participation for women.  We will also examine what influence HIV serostatus disclosure to sexual partners has on these effects.  See Figure 1.    
We have a secondary aim to compare operational outcomes across study arms.   We will compare  counseling time required, proportion of women returning for ongoing counseling at 6 and 10 weeks, clients perceived quality of services and the cost of service provision and opportunity cost incurred by client across the two arms.  This aim will be achieved through analysis of clinic records including counseling log forms and financial records. 

D.2. Study Site and Population

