D.5.2. Intervention Components:  The intervention is staged to handle key decisions that antenatal women need to make including: 1) Whether to test for HIV; 2) Whether to receive HIV test results; 3) Whether to enroll in PMTCT programs and accept ARV prophylaxis; 4) Whether to share HIV test results with sexual partners and encourage partner uptake of HIV VCT; 5) Decisions regarding infant feeding choices and; 6) Decisions regarding family planning choices.  The intervention is also designed to address factors that both HIV-positive and HIV-negative women face at each stage.  Prior to receiving the HIV test, women will be provided with information to better inform these key decisions through a standardized health-education video and a pre-test counseling session.  The first post-test counseling session will focus primarily on the decisions that women need to make shortly after learning their HIV serostatus and before they deliver their child, namely disclosure of HIV status to sexual partners, acceptance of ARVs, PMTCT participation and infant feeding choices.  The next two post-test counseling sessions will revisit these decisions, and will add a focus on legal education and referral, partner testing, sexual risk behavior, and family planning.  These key decisions will be reinforced through support groups to which women are actively referred. Women in the control group will receive standardized post test counseling according to the protocol recommended by WHO/CDC. Women in the control group will also receive additional post test counseling sessions; these sessions will also occur at the 6 and 10 week follow up visit and will focus on infant health.  Table 1 below compares the intervention components by study arm, and describes how they differ by HIV serostatus in the intervention arm.   The shaded text in this table indicates the counseling that will be handled by the existing clinic staff.  All of the other counseling will be handled by the counselors hired specifically for this research study.   

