D.6. Feasibility of the intervention:  When designing the experimental intervention to be tested in the proposed study we were sensitive to the fact that there is currently a standard protocol for HIV VCT that has been endorsed by WHO and CDC and is widely accepted and utilized in the field.  Our intervention builds on the strengths of these existing protocols.  The need to create a feasible intervention must be balanced with the need to create an intervention that is intense enough to have an impact.  We have designed a model of counseling and post-test support that does not require complex reorganization of VCT and PMTCT services.  The video will be shown to women as part of their group HIV-pretest counseling session.  We will extend the length of the pre-test counseling session by about 30 minutes to cover issues related to disclosure and PMTCT participation.  The first post-test session will be lengthened by an additional 20-30 minutes for both HIV-positive and HIV-negative clients.  There will be two additional 30-45 minute post-test counseling sessions for women that coincide with their 6-week and 10-week post-partum visits.  We designed the intervention to take advantage of the fact that women are already returning to the Family Clinic at regular intervals for the immunization of their children.  Finally, HIV-infected women will have the option to enroll in post-test support groups facilitated by our staff psychologist..  We feel that in order to effectively counsel women through all of the issues that they face when learning of their HIV status, this additional counseling time and post-test support is warranted.

  

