D.7. Comparison Condition:  The comparison arm is designed to provide standard of care for HIV VCT.  Currently, the VCT that has been provided by Umlazi Section D ANC since 2001 is in accordance with the National VCT guidelines established by the South African Department of Health.  These national standards are based on the international standards established by WHO and CDC and also take into account the cultural context of South Africa. There are four full-time HIV counselors and five professional nurse counselors in the clinic.  All counselors have received training in HIV VCT as per the South African national standards.  Women in the comparison arm will meet with research counselors at the 6 and 10-week postpartum visits.  To minimize any bias that may be associated with contact time with counselors, the 6 and 10-week counseling sessions for women in the comparison arm will be comparable to the length of sessions for women in the intervention arm.  This will provide women with an opportunity to talk about concerns that they may have about their health of the health of their infant.  In their introductory remarks, the counselors will indicate that the primary focus of the session is on infant health.  Because these sessions, like all others, will be client-centered, it is possible that women in the comparison arm will raise questions that are similar to the issues being discussed with women in the intervention arm, namely disclosure, partner testing, and family planning.   Counselors have an ethical obligation to respond to these issues when raised by the women.  The counselors will use skills that are part of the standard skill set of counselors at the clinic, including actively listening to women's concern's, responding empathetically, and offering referral information when appropriate.   The counseling tools that we use for women in the intervention arm, for example the disclosure role-play scenarios, will not be used when counseling women in the comparison arm on disclosure.     
  

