D.8.2.3. Quality of counseling as perceived by the woman: We will ask 5% of women randomly sampled using exit interviews after their counseling sessions about their perception of the counseling quality that they received.  They will be asked to evaluate the following skills of the counselors viz.  listening, responding with concern and support, supporting decisions and making appropriate referrals using a five-point scale, one being weak and five being strong. In addition, at the 14 week and 9 month assessment, we will ask about their perceived quality of care.   

D.8.2.4. Costs of the standard VCT and the VCT plus post-test support: We will gather information on costs of the intervention from the clinic and the client's perspectives.  We will quantify costs of each element of the counseling and testing process. This will be done through financial records from the clinic.  We will ask clients on the 9-month follow-up survey about costs they may have incurred accessing the services including transportation costs and wages lost during the period of time participants were in the clinic.  

D.8.3. Independent/Predictor/Mediating Measures
D.8.3.1. HIV Serostatus:  We will gather information on women's HIV serostatus from the ANC records.  We have powered the study to be able to stratify all of our analyses by serostatus.  

D.8.3.2. Demographic:  Basic demographic characteristics of participants including age, marital status, educational level, and socioeconomic status will be gathered.  Socioeconomic status will be measured by indicators such as type of roofing and flooring, type of toilet facilities and ownership of radios and televisions.  

D.8.3.3. Parity:  We will ask women about the number of pregnancies that they have had in the past and the number of children who are currently living.  For women who report that they have children we will ask whether any of the children are HIV-infected.  

D.8.3.4. Disclosure to sexual partners: To measure the rates of HIV serostatus disclosure to sexual partners we will ask women who return for the survey interview 9-months post-partum whether they have shared their HIV test results with their primary sexual partner.  

D. 8.3.5. Duration of time since testing:  We will assess the gestational age at which women received testing and the gestational age at delivery to calculate the duration of time between testing and post-intervention assessment.  This information can be gathered from clinic records.  

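### The comparison arm's length-matched 6- and 10-week research sessions make the Aim 3 across-arm contrast understate the counseling time added over standard VCT, and the named cost source is not shown to cover study and partner staff

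*Protocol*

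**What the plan says.** The secondary aim compares operational outcomes across study arms, including "a) counseling time required; (b) the proportion of women returning for ongoing counseling at 6 and 10 weeks", and also the cost of service provision. The title of D.8.2.4 sets standard VCT against VCT with post-test support. It promises to cost each element of counseling and testing, and names the source: "This will be done through financial records from the clinic".

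D.7 opens with "The comparison arm is designed to provide standard of care for HIV VCT". It then has comparison women meet research counselors at 6 and 10 weeks. The reason given is "To minimize any bias that may be associated with contact time with counselors", and the consequence is that the 6- and 10-week "sessions for women in the comparison arm will be comparable to the length of sessions for women in the intervention arm". D1 describes the comparison arm differently: women "will have brief follow-up sessions with counselors 6- and 10-weeks postpartum".

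For the intervention arm, D.6 states: "There will be two additional 30-45 minute post-test counseling sessions for women". On staffing, D.5.2 says that existing clinic staff handle the counseling shaded in Table 1, and adds: "All of the other counseling will be handled by the counselors hired specifically for this research study". A staff psychologist runs the support groups (D.5.2.7), and the university law clinic supplies the on-site legal service (D.5.2.8). D.8.2.1 has counselors log the start and end of every session in both arms.

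**The concern.** One comparison arm is asked to do two jobs. For efficacy it should match the intervention in contact time, so that content and not attention explains any difference. For Aim 3 it should stand for what a clinic does now. The matched sessions serve the first job and defeat the second, because they remove from the time contrast the two longest additions in the package.

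The standard post-test protocol summarised in D.5.2.3 has four components in a single session and no postpartum counseling. The 6- and 10-week immunization visits are routine (D.2.1), but nothing describes counseling of this length at them as routine.

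The Human Subjects section expects the intervention to be cost-effective, sustainable and easily disseminated. A clinic deciding on adoption needs the extra staff time and cost over its present service. As written, Aim 3 would report the extra over a service that no clinic provides, and would draw costs from records that may not include the people who deliver the package.

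**Working it through.** The protocol states no total counseling time, unit cost or expected difference, so there is no figure of its own to reproduce. The check is arithmetic on its session lengths.

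**Inputs (minutes)**
- Extra pre-test time: about 30 (D.6) or about 15 (D.5.2.2).
- Video: about 30 (D.5.2.1). D.6 shows it within the group pre-test session and does not say whether the 30-minute extension includes it.
- Extra first post-test time: 20-30 for all women (D.6); or 10-15 for all plus 15-20 for HIV-positive women, that is 25-35 for the latter (D.5.2.3).
- Added sessions: two of 30-45, that is 60-90 (D.6).
- Comparison-arm sessions: the same 60-90 if matched (D.7).

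**Formulas**
- Increment over standard VCT = extra pre-test + extra first post-test + two added sessions.
- Increment visible between arms = that increment minus the two comparison sessions.
- Share hidden = two comparison sessions / increment over standard VCT.

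**D.6 figures, matched length**
- Increment: 30 + 20 + 60 = 110, up to 30 + 30 + 90 = 150.
- Visible: 30 + 20 = 50, up to 30 + 30 = 60.
- Share hidden at the four corners: 60/110 = 55%, 60/120 = 50%, 90/140 = 64%, 90/150 = 60%.
- Midpoints: 75/(30 + 25 + 75) = 75/130 = 58%.

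**Other lengths in the protocol, still matched**

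| Reading | Lowest share | Highest share |
|---|---|---|
| Pre-test +15, D.6 post-test | 60/105 = 57% | 90/125 = 72% |
| Pre-test +15, D.5.2.3, HIV-negative | 60/90 = 67% | 90/115 = 78% |
| Pre-test +15, D.5.2.3, HIV-positive | 60/110 = 55% | 90/130 = 69% |
| Video 30 and pre-test +15, D.6 post-test | 60/135 = 44% | 90/155 = 58% |
| Video 30 and pre-test +30, D.6 post-test | 60/150 = 40% | 90/170 = 53% |

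The hidden minutes are 60-90 in every row; only the denominator changes. Support groups are left out because their length and attendance are not given. If one 60-minute attendance (assumed) counted as counseling time, the D.6 share would be 60/180 = 33% to 90/200 = 45%.

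**Comparison sessions brief, as in D1.** Assume 5-20 minutes each, D.6 figures otherwise: 10/150 = 7% at the least, 40/110 = 36% at the most.

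**Cost.** No wage, unit cost, support-group attendance or legal-service cost is given, so no percentage follows. The direction can be stated. Support groups, legal staff and the video are intervention-only resources and do not cancel. If all staff are costed, the share hidden by matching is therefore smaller for cost than for time. As an illustration on the D.6 midpoints, intervention-only resources worth 20 counselor-minutes per woman bring the share to 75/150 = 50%, and 60 minutes bring it to 75/190 = 39%.

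**The case against.** The length matching is a reasoned attention control with its purpose stated, and removing it would harm the efficacy comparison. That stands, and nothing here asks for its removal.

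Standard VCT is also the protocol's label for the comparison arm: D.4.4 randomizes to it by that name. Aim 3(b) compares return for 6- and 10-week counseling, so those sessions belong to the operational comparison by intention, and a contrast with no such sessions is a different estimand. This is fair for Aim 3(b). It does not settle time and cost, because D.7 presents the arm as standard of care while adding research-only contact, and nothing in the protocol says which sessions count.

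No data are lost, since the logs are kept per session. That is correct. It makes the repair cheap, but the specified contrast is still the unadjusted one.

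A reader might infer three stronger things that the protocol does not support:
- **That the clinic's books omit the research staff.** No section says so. It is an inference from D.5.2, D.5.2.7 and D.5.2.8. D1 counts the counseling logs among clinic records, so the term may be meant broadly. What stands is that coverage is not shown.
- **That cost, like time, is understated by more than half.** Nothing in the protocol allows a figure for cost.
- **That the two problems add up for cost.** If the books did omit research staff, the matched sessions would cost nothing in either arm, and matching them would not alter the cost contrast.

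**Conclusion.** The concern holds for time as a matter of design. Under D.7, the across-arm contrast hides 60-90 minutes per woman of the counseling the package adds over standard VCT. On the D.6 lengths that is 50-64% of the increment, about 58% at midpoints; with the other lengths and the video it is about 40-78%. More than half is therefore likely on D.6 but not certain. The figures assume that women attend both sessions, that the matching is exact and that support-group time is not counted. They fall to 7-36% if the D1 description applies, on the assumed 5-20 minutes. The conflict between D1 and D.7 must be resolved whichever is meant, because it decides what Aim 3(a) measures.

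For cost, two limited statements stand. The comparator includes research-only sessions, and the named source is not shown to cover the study-hired counselors, the psychologist or the law-clinic staff. Neither can be given a size. The outcomes are secondary and the logs preserve the data, so the fault lies in how the comparison is specified and can be corrected.

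**What to change.** - **Aim 3(a) and 3(d):** state that time and cost are reported against standard VCT, with the comparison arm's 6- and 10-week research sessions excluded by means of the per-session logs. Report the as-delivered across-arm contrast alongside. Keep the attention control and Aim 3(b) as they are.
- **D.8.2.4:** add study and partner expenditure, combined with logged minutes, as a cost source, so that research counselors, psychologist, legal staff and video are all valued.
- **Session lengths:** reconcile D1 with D.7 on the comparison sessions, and D.5.2.2 and D.5.2.3 with D.6 on the added pre-test and first post-test time. Say whether the video falls within the pre-test figure.

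The cost is protocol wording, a little more analysis of the logs, and the retrieval of study and law-clinic expenditure. What participants receive does not change. The stated time and cost of the intervention will probably look less favourable.
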